## Methods

### Trial design

The two testing trials will be performed according to a randomized crossover design. Subjects will be allocated to one of the two intervention groups according to a prepared randomization list and will at this time be unaware of group to which they are allocated. Implementation of the random allocation sequence will be done via central telephone to provide allocation concealment. The flow chart of the study is described in Figure 1.

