### Intervention

The aims of the study are to investigate (1) whether continuous endurance exercise or high-intensity intermittent endurance exercise in water elicits both a higher release of ANP and BNP and a higher plasma concentration of glycerol, and (2) to determine if continuous endurance exercise in water or high-intensity intermittent endurance exercise in water leads to a more pronounced short term (that is, 2 hours) EPOC effect.

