### Overview

Twenty healthy sedentary pre-obese and obese class-1 men with BMI ranging from >30 kg/m^2^ to <34.9 kg/m^2^ according to WHO 2004, will be scrutinized with regard to their metabolic responses to continuous exercise in water and to high-intensity endurance exercise in water. Both trials will be matched for energy expenditure. After preliminary testing, the tests will be conducted as repeated measurements, with 72 hours of separation time in between. The two different exercise protocols will be compared.

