### Statistical methods

Figures will be presented as means ± standard error of the mean (SEM). Differences in outcomes among the groups will be tested by analysis of covariance (ANCOVA). For statistical significance (*P* <0.05), multiple comparisons will be adjusted for using the Tukey test.

Our assumptions for the power calculation are mainly based on the results of Fenzl *et al*. [18] who recently reported an increase of ANP from 29.8 ± 3.4 pmol/l to 82.5 ± 8.3 pmol/l. Assuming an increase from 35 to 55 with a SD of 10, we would need eight patients in each group to achieve 90% power at the 1% significance level (two-sided test). With an assumed drop-out rate of two in each group, we need 20 persons in total.

Hormone values that are expected to rise during the recovery period of the exercise include catecholamines, ANP, BNP, glycerol and free fatty acids. Differences in these hormones between high-intensity intermittent exercise protocols compared to less intense protocols have not yet been analyzed; studies investigating intermittent bouts of exercise results were in contrast to moderate continuous exercise of the same duration. Different scores relative to the contribution of fat oxidation for repeated trials (77.6% ± 2.7%) versus single trials (62.1% ± 5.7%) were computed in the study of Goto *et al*. [11]. A test would require less than 10 subjects in each group, assuming a similar response to water immersion. Matsuo *et al*. [19] demonstrate that EPOC was greater when high-intensity interval training was conducted compared to aerobic types of exercise. For the power calculation, eight subjects in each group should be included into the study.

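### The stated 90% power is for what appears to be a rise in ANP in two independent groups, so it is not a power figure for the within-man comparison of two exercise protocols

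*Protocol article*

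**What the plan says.** Design and question (protocol article):

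- Trial design: "The two testing trials will be performed according to a randomized crossover design".
- Overview: "the tests will be conducted as repeated measurements, with 72 hours of separation time in between", and "The two different exercise protocols will be compared".
- Intervention, first aim: "whether continuous endurance exercise or high-intensity intermittent endurance exercise in water elicits both a higher release of ANP and BNP".

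Sample size (protocol article, Statistical methods):

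- The empirical basis is a cited study that "reported an increase of ANP from 29.8 ± 3.4 pmol/l to 82.5 ± 8.3 pmol/l".
- The calculation is: "Assuming an increase from 35 to 55 with a SD of 10, we would need eight patients in each group to achieve 90% power", two-sided at 1%.
- The total is: "With an assumed drop-out rate of two in each group, we need 20 persons in total".
- The same section says that differences in these hormones between high-intensity intermittent and less intense protocols have not been studied so far.
- A further remark contrasts fat oxidation in repeated and single exercise bouts (77.6% versus 62.1%) and concludes that fewer than 10 per group would do, without power or alpha.
- The EPOC paragraph ends: "For the power calculation, eight subjects in each group should be included into the study". No effect size, SD, alpha or power is given for it.

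The analysis in that section uses P <0.05 with a Tukey adjustment, not the 1% of the calculation. ANP is one of the primary outcomes.

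**The concern.** Two features of the calculation do not match the trial.

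The first is the effect. The trial asks whether one protocol releases more ANP than the other. Both protocols are exercise in water, which the Background says augments ANP release, so both should raise ANP. The quantity of interest is the difference between two responses. The calculation uses an increase, introduced straight after a cited increase, and assigns no value to the difference between protocols.

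The second is the design. Each man does both protocols, so precision depends on the SD of the within-man difference. The calculation uses an SD of 10 as if two separate groups were compared.

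This is the only complete power statement in the article, and it concerns a primary outcome. If the two protocols show no clear difference in ANP, a reader will assume that the trial had 90% power to separate them. The calculation gives no such assurance.

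**Working it through.** **Inputs from the document:** difference 55 − 35 = 20; SD 10; two-sided alpha 0.01; power 90%; drop-out 2 per group. No unit is attached to 35, 55 or 10; pmol/l is taken from the cited figures.

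**Not in the document, assumed here:** SD 10 applies to each session, and the correlation ρ between a man's two sessions lies between 0 and 0.7.

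**Step 1. Reproduce the plan's figure.** Two independent groups, normal approximation:

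n = 2(2.576 + 1.282)² / (20/10)² = 7.44, rounded up to 8 per group.

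The total is 2 × (8 + 2) = 20. Both stated numbers reproduce. With 8 per group the normal approximation gives 92.3% power.

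**Step 2. The same parallel-group comparison with a t-test** (noncentral t, alpha 0.01): 8 per group gives 82.6%, 9 gives 88.8% and 10 gives 92.9%. So 90% would need 10 per group. At alpha 0.05, 8 per group gives 96.0%.

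**Step 3. The comparison that the trial makes.** In a two-period crossover with n completers:

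- SD of the within-man difference = 10 × √(2(1 − ρ))
- noncentrality = difference / (SD of difference / √n), with n − 2 degrees of freedom

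Twenty men less 2 drop-outs in each of two groups leaves n = 16. At ρ = 0, for example, the SD of the difference is 10 × √2 = 14.1, and the noncentrality for a difference of 20 is 20 / (14.1/4) = 5.7.

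| ρ (assumed) | SD of difference | Detectable with 90% power, 1% / 5% (pmol/l) | Power for 10 pmol/l, 1% / 5% | Power for 5 pmol/l, 1% / 5% |
|---|---|---|---|---|
| 0 | 14.1 | 15.5 / 12.3 | 47% / 75% | 9% / 26% |
| 0.3 | 11.8 | 13.0 / 10.3 | 66% / 88% | 14% / 35% |
| 0.5 | 10.0 | 11.0 / 8.7 | 83% / 96% | 21% / 46% |
| 0.7 | 7.7 | 8.5 / 6.8 | 97% / 99.8% | 38% / 67% |

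For a between-protocol difference of 20 pmol/l, power at 1% is 99.1% at ρ = 0 and higher at every larger ρ in the table.

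If all 20 men complete, the difference detectable with 90% power falls to 13.5, 9.5 and 7.4 pmol/l at 1% for ρ = 0, 0.5 and 0.7.

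**The case against.** Several points on the other side are sound.

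- **The effect might be the right contrast.** The text does not say that 35 is a resting value. If 35 and 55 were meant as ANP under the two protocols, the contrast would be correct. But the word used is increase and the cited basis is an increase, so a rise with exercise is the natural reading, though still an inference. On the other reading the 20 has no source, since the same section says such differences have not been studied, and the formula is still for independent groups.
- **The independent-groups formula is conservative.** This stands. For the same 20 pmol/l, 16 crossover completers have at least 99% power at 1%, against 82.6% for 8 versus 8 by t-test. The choice of formula understates power; only the choice of effect can hurt.
- **The word group can have a meaning.** A two-period crossover has two sequence groups, and Trial design refers to two intervention groups. Ten men per sequence with two lost from each would give the 16 completers used above. The valid criticism concerns the variance and the effect, not the word itself.
- **Eight is also a paired-test answer.** A paired t-test with SD of change 10 needs 8 men for 90% power at 1%. But doubling to 16 and adding drop-outs to each group show that two groups were meant.
- **The fat-oxidation remark does compare exercise patterns.** It does, and it relates to the respiratory exchange outcome. It is not about ANP and states no power or alpha, so it does not repair the ANP calculation.
- **The t-test result in step 2 is secondary.** This also stands. It describes a parallel design at 1%, which is not how the trial will be run.

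An article may condense a protocol, but this calculation is given in full: effect, SD, alpha, power, number and drop-out. The mismatch is in what is stated, not in what is left out.

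**Conclusion.** The point holds as a mismatched power statement. The arithmetic reproduces, but it answers a different question: apparently a rise in ANP, in two independent groups. The 90% cannot be carried over to the within-man comparison of continuous and intermittent exercise, because neither the expected difference nor its SD is given.

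A reader might infer that the trial is underpowered. The documents do not support that. Under SD 10 per session and correlation 0 to 0.7, the same 20 men give very high power for 20 pmol/l, moderate to high power for 10 and low to moderate power for 5. Nothing in the article says which of these differences is realistic or relevant. Low power figures for two parallel groups of 8 would not apply either, since the trial is a crossover.

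A reader might also infer that a null result would be declared as equivalence. No such conclusion is planned. The risk is only that the 90% is taken at face value when the result is read.

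The detectable differences rest on the assumed SD and correlation. SD 10 is no better sourced for the between-protocol contrast than for the increase.

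**What to change.** Keep 20 men, with 16 expected completers, and replace the power sentence by one for the crossover contrast. It should state:

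1. the between-protocol ANP difference detectable with 90% power;
2. the SD per session and the within-man correlation, labelled as assumptions and given with a range;
3. one alpha, the same in the calculation and the analysis, since the section now sizes at 1% and tests at P <0.05;
4. whether group means sequence group.

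Possible wording: *With 16 completers the crossover has 90% power, at a two-sided 5% level, to detect a between-protocol difference in ANP of 8.7 pmol/l, assuming SD 10 per session and within-man correlation 0.5 (12.3 to 6.8 pmol/l for correlations 0 to 0.7).* If 1% is kept, the figures are 11.0 pmol/l, with range 15.5 to 8.5. The choice of alpha should take account of the several primary outcomes and the planned Tukey adjustment.

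For EPOC, either remove the eight per group or give a detectable EPOC difference in the same way.

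The cost is one rewritten paragraph. It needs no more men and no change to the design or schedule, and the Trials status section says that recruitment has not begun.

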### Trial-specific preventive measures and duties

Participants will be informed about any risks and the trial process both verbally and in written form.

### Duties on the part of the investigator

It is hereby confirmed that ethical and scientific criteria as well as quality standards in terms of planning, trial procedure, monitoring, analysis and documentation of the trial will be fully observed and carried out in accordance with the protocol. All rights of the participants will be respected and the results of the trial will be handled correctly. The investigator and applicant are responsible for the wellbeing and health protection of the participants. The investigator also commits to carry out the trial according to the trial protocol and to report and document deviations to the sponsor and the ethics committee.

### Statement regarding damage coverage

The sponsor compensates the participant for any damage suffered during the clinical trial. In order to cover possible costs, insurance will be procured. The sponsor of the trial approves full compensation to all participants of the trial also beyond the coverage of the liability insurance.

### Ethical principles

#### Evaluation of the risk-benefit ratio

The paper will be considered a preventive contribution for obese persons. The evidence of the aqua-intervention with regard to weight reduction and weight stabilization will be worked out. Existing interventions will be further improved according to the criteria of evidence-based medicine by choosing the right exercise protocol. Health-related recommendations can only be made once the physiological basis for substrate utilization has been established and a qualitative verification of the fat oxidation has been carried out. Measurements of the partial pressure of oxygen and carbon dioxide in water are routine, and so is the measurement of the arterial oxygen saturation. The examination rooms in the Medical Center permit standardized relaxation and defined exercise tests on the Reha Aquabike. All the planned interventions are justifiable and reasonable from a medical point of view. The measurements are non-invasive and painless. In water every participant will be protected from possible drowning by an air-filled ruff. So far, no accident has been reported worldwide.

#### Patient informed consent

Previous to study participation patients receive written and spoken information about the content and extent of the planned study, for instance, about potential benefits for their health and potential risks. In the case of acceptance, they sign the informed consent form.

#### Description of risks

Exercise testing is not without risk. Under controlled conditions an increase of heart rate and oxygen uptake is concomitant with the increased workload. In the event of undetected myocardial disease the heart may not be sufficiently supplied with blood. Symptoms such as sudden pallor, sweating, chest discomfort, or nausea have to be reported immediately.

The risk of undetected coronary heart disease and sudden death will be reduced to a large extent by the preliminary medical check-up. The risk increases with age, therefore, the age limit is 50 years. A defibrillator will be available. Moreover, the standard emergency equipment required for ergometry laboratories will be available. Trials will only be conducted with healthy subjects without detected risk factors. A doctor on-call will be available in the medical center at all times, who will be informed about the upcoming exercise test. Taking blood samples is part of the discomfort and risk involved in ergospirometry. In addition to a little twitch and subsequent small hematomas, circulatory instability may occur. Blood samples will be taken while the subject is in a semi-reclined position, which stabilizes the circulation. Infection, thrombosis or lesions of tissue or nerves are rare side effects and can be almost excluded when blood samples are taken by well-trained staff. An inflatable ruff prevents drowning if the subject becomes unconscious during the trial. The subjects will be continuously monitored.

#### Benefit for the subject

Subjects will not be given compensation in money. The individual results of the ergospirometry, ECG, and pulmonary function test will be discussed in detail with the subjects; extensive consultations about adequate health-oriented training recommendations will be given. Subjects will receive meaningful additional information about their current level of performance by parameters assessed by invasive methods (lactate, et cetera). Thus subjects will receive reliable information concerning their current state of health. Moreover, recommendations on the individual effects of water immersion and exercise modalities will allow participants a more targeted use of water as a medium. Until now, recommendations have been given only on an empirical basis, following across-the-board dosage criteria.

#### Vote of the ethics committee

The study protocol was approved by the ethics board of the Kanton St. Gallen on March 14, 2011 (EKSG 11/026/2B).

### Quality control and quality assurance: description of measures

#### Data security/disclosure of original documents

Gathered data will be stored in anonymized form only and will be used exclusively for this trial. No conclusions can be drawn about the person affected. Each subject will be assigned an identification code, which will be kept on a separate datasheet. This code will be used during the entire trial. Personal data allowing identification of the subjects will be deleted. In addition to all members of the research staff who are bound to their professional obligation to discretion, all members of the ethics committee may have access to the data at any time. All documents and data storage media containing encrypted personal data will be stowed in locked storage. The laptop computer used in the trial will be protected by a password in order to prevent access from unauthorized persons. A personal firewall will be installed by the internal information technology (IT) provider. Data will be stored in databases, mainly as Excel files. The trial can be reconstructed using the encrypted data. Original files, such as protocols, will be stored with care. All relevant data will be transferred to the digital data-entry form. Thus, all results of the trial can be retraced for a five-year period on the internal server, which is protected by a password. All data on the laptop computer will be erased by the internal IT provider.

## Trials status

The recruitment of subjects has not yet started.

## Abbreviations

ANP: Atrial natriuretic peptide; AR: Adrenergic receptor; BMI: Body mass index; BNP: Brain natriuretic peptide; cAMP: Cyclic adenosine monophosphate; cGMP: Cyclic adenosine monophosphate; CO2: Carbon dioxide; DXA: Dual-energy x-ray absorptiometry; ECG: Electrocardiogram; EPOC: Post-exercise oxygen consumption; FEV1: Forced expiratory volume; FFA: Free fatty acids; HR: Heart rate; IAT: Individual anaerobic threshold; MVV: Maximum voluntary ventilation; NP: Natriuretic peptide; NNPR-C: Natriuretic peptide receptor type C; NYHA: New York Heart Association; O2: Oxygen; PAR-Q: Physical Activity Readiness Questionnaire; PKG: CGMP-dependent protein kinase; RER: Respiratory exchange rate; RPE: Rating of perceived exertion; WHO: World Health Organization.
